## Abstract

**Background:**

Psychosocial problems are more prevalent among patients with chronic diseases than among the general population. They may lead to a downward spiral of poor adherence, deterioration of the condition and decline in daily functioning. In addition to medical management, systematic attention to emotional and role management tasks during routine chronic care seems mandatory. We intend to integrate an existing nurse-led minimal psychological intervention to support patients’ self-management, which appeared to be effective and cost-effective, in routine care by primary care nurses, so we adjusted it to fit the host setting. The resulting Self-Management Support (SMS) programme involves early detection of patients with emotional distress and problems of daily functioning, as well as self-management support through problem solving and reattribution techniques. Strategies to embed SMS in daily practice include training and booster sessions for practice nurses as well as organisational and financial arrangements. This study aims to simultaneously evaluate the implementation process and effects of SMS in routine care, using a hybrid effectiveness–implementation design.

**Methods/Design:**

Registration data, questionnaires and interviews will be used to explore the facilitators, barriers and costs regarding successful implementation of SMS. The effects of SMS will be evaluated in a pragmatic cluster-randomised controlled trial with a baseline measurement and follow-up measurements after 4 and 12 months. The population will consist of 46 practice nurses and their type 2 diabetes patients (N = 460; 10 per practice nurse). The practice nurses will be randomly assigned to the intervention or control group. Practice nurses of the intervention group will receive SMS training. Patients for the intervention and control groups will be recruited by a researcher-led self-administered screening procedure to decide which patients of those scheduled for routine consultation are likely to be detected by the practice nurses as eligible for the self-management support. Primary outcome measure is patients’ daily functioning. Secondary measures include emotional well-being, participation, autonomy and control over the disease.

**Discussion:**

Our hybrid study design is complicated by the detection method used by the practice nurses. This method is an implementation issue in itself that has consequences for the realisation and power of the effect evaluation.

**Trial registration:**

Current Controlled Trials, NTR2764

## Background

The prevalence rate of psychosocial problems is higher among patients with chronic somatic diseases than among the general population [1-4]. Problems like depression or distress may hamper the ability to manage a chronic condition [5]. A reciprocal relationship has been suggested: emotional distress may interfere with control over the disease, and at the same time, poor control over the disease can lead to emotional distress. Persistent negative feelings have implications for adherence to medication and lifestyle regiments, motivation, self-efficacy and problem solving [6,7]. Patients therefore face not only the day-to-day medical management, but also the challenge to deal with their emotions and problems of daily functioning in order to remain in control of their illness [6,8]. To improve the outcomes of chronic care, Lorig and Holman argue that three self-management tasks should be addressed in primary care: medical management, emotional management and role management [8]. However, Dutch guidelines for the care of chronic diseases like type 2 diabetes mellitus primarily focus on medical and lifestyle management [9,10]. This seems too narrow a focus, as there is also room for improvement in the detection and treatment of emotional problems in the chronically ill [4,11,12].

Our study intends to facilitate a shift towards a chronic care approach that combines attention to both biomedical and psychosocial aspects. We believe that equipping practice nurses (PNs) with the ability to provide this might be an effective way to realise such a biopsychosocial approach in chronic care [13]. PNs in the Dutch primary care setting see patients on a regular basis, as they have the task of providing routine check-ups [14]. Since diabetes patients were the first to be cared for by PNs, we aim to integrate an existing nurse-led minimal psychological intervention (MPI) in the diabetes follow-up care by PNs. The nurse-led MPI has proved to be effective in supporting the self-management skills of diabetes and COPD patients with minor to moderate depression [15-18].

The MPI can only be adopted by PNs if a detection method is added that enables PNs to distinguish between patients who are active self-managers, patients who would benefit from the psychosocial support, and patients who need more specialised psychosocial diagnostics or treatment. We call the resulting stepped approach to detection and treatment ‘Self-Management Support’ (SMS). In addition to adapting the MPI to become SMS, we need to arrange for a training course with booster sessions, and ensure the allocation of time and organisational support to enable the PNs to adopt SMS in their current practice. For a thorough understanding of the effectiveness of SMS, the facilitators and barriers to its implementation in routine care need to be taken into account. Therefore, we want to start a hybrid effectiveness–implementation trial to examine the effectiveness of SMS in terms of patient outcomes, and focus on implementation outcomes.

### Aim

The aim of our study is to evaluate the process and effectiveness of SMS implemented as an integral part of the care for patients with type 2 diabetes mellitus provided by PNs. We will simultaneously address the following research questions:

1. *What is the uptake of the SMS programme by the practice nurses, and what barriers hamper the implementation of SMS in routine primary care?* (Study of the implementation strategies for SMS.)

2. *What is the effectiveness of SMS in terms of daily functioning, emotional health status, social participation, self-management behaviour, and health care use by patients with type 2 diabetes?* (Study of the SMS clinical intervention.)

The effectiveness of SMS (question 2) will be considered while taking the barriers to the implementation process (question 1) into account.

## Methods/Design

In our study, we will use a hybrid effectiveness–implementation design to focus on implementation issues and the effectiveness of SMS at the same time. Curran and colleagues have presented a continuum of three types of such hybrid effectiveness–implementation (E-I) study designs [19], ranging from effectiveness research with minimal implementation strategies (type 1) to designs where effectiveness and implementation are equally balanced (type 2) and an implementation approach with minimal focus on effectiveness outcomes (type 3). We will examine the effects of SMS on patient outcomes and simultaneously focus on implementation outcomes, hence it is a type 2 hybrid E-I study design.

Below, we first describe our implementation strategies (intervention) and then explain our evaluation methods regarding the implementation and effects of SMS in routine care (evaluation).

### Intervention

In a previous study, the nurse-led minimal psychological intervention (MPI) was carried out by trained research nurses [20]. In our present study, practice nurses who provide diabetes care will have to adopt the MPI in their current practice. This required changes with regard to the clinical intervention as well as the organisational context in which the intervention will be integrated [21]. This section explains the steps that will be taken to implement the resulting SMS in routine diabetes care.

#### Implementation strategy 1: adaptation of clinical intervention

The nurse-led MPI has been altered from a ‘research object’ to an intervention that can be systematically embedded in routine primary care. Adaptations were needed regarding the target group, providers, detection of eligible patients and self-management support. The shift from MPI to SMS is summarised in Table 1.

**Table 1 T1:** The SMS approach contrasted with the original MPI

	**MPI**	**SMS**
Target group	Chronic patients with mild or non-severe major depression	Chronic patients with emotional distress and problems of daily functioning
Providers	Research nurses not involved in usual care	Practice nurses providing usual chronic care
Diagnostic approach	For research purposes. Using an extensive diagnostic interview, following strict psychiatric criteria	As part of daily care. Using simple tools, following a stepped care approach that fits the primary care setting
Self-management support intervention	1. cognitive therapy (reattribution)	1. problem solving
	2. problem solving	2. cognitive therapy (reattribution)

##### Target group

The original effective nurse-led MPI was provided specifically to patients with a diagnosis of depression, whereas a wide range of psychological and social problems occur in a routine primary care setting. What primarily matters in daily practice is to what extent patients experience problems of daily functioning [12]. SMS was therefore designed for chronic patients who encounter problems of daily functioning and emotional distress.

##### Providers

Instead of research nurses providing the intervention as an add-on to usual care, SMS will be integrated in usual care provided by PNs. PNs work in general practice under supervision of a GP. They see type 2 diabetes patients every 3 months for a diabetes check-up. SMS is to become an integral part of these check-ups.

##### Detection procedure

The diagnostic procedure that was used to recruit patients for the study to evaluate the original MPI is not feasible in routine primary care: it was limited to depression, and included an extensive and time-consuming diagnostic interview (the Mini International Neuropsychiatry Interview) to confirm a diagnosis of depression according to psychiatric criteria. For SMS, PNs will have to decide during routine diabetes check-ups whether watchful waiting, offering psychosocial self-management support or a referral to the GP because of symptoms of mental health problems is most appropriate. Therefore, we have introduced a stepped approach that allows interventions not sooner or more intense than necessary and not later or less intense than required. The approach is as follows. During each regular diabetes check-up, PNs will explore whether the patient is experiencing problems in daily life. Then they verbally administer the ‘Daily Functioning Thermometer’ (DFT), a visual analogue scale to rate the overall burden of diabetes. (See the Measurements section below for more information about the instruments.) Practice nurses will also verbally administer the 3-item Distress Screener (DS), a quick-scan instrument for emotional distress and an indicator of potential underlying severe mental health problems [22]. Patients with DS > 3 will be asked to complete the Four-Dimensional Symptom Questionnaire (4DSQ) [23] immediately after the consultation. This self-report measure is widely used in Dutch primary care to distinguish non-specific general distress from depression, anxiety and somatisation. Scoring the 50 items of the 4DSQ should take 5–10 minutes The completed 4DSQ will be returned to the PN, who will score the 4DSQ using a scoring form. Patient’s scores on the 4DSQ will distinguish between mild, moderate and severe mental health problems. Patients who experience problems of daily functioning (DFT > 4) and emotional health problems (DS > 3 combined with moderate scores on subscales of the 4DSQ) will receive self-management support from the PN. If a patient has only ‘mild’ scores on the 4DSQ, the PNs will opt for watchful waiting. The same option will be used for patients with moderate scores on the 4DSQ who do not report problems of daily functioning due to diabetes (DFT ≤ 4). These patients will be informed by telephone that there is as yet no indication for extra consultations. Patients with a ‘severe’ score on at least one of the subscales will be referred to the GP. The detection protocol is summarised in Table 2.

**Table 2 T2:** Detection protocol

	**DFT** ≤ **4**	**DFT > 4**
DS ≤ 3	No indication	Watchful waiting
DS > 3	On the basis of the 4DSQ:	On the basis of the 4DSQ:
	Mild: watchful waiting	Mild: watchful waiting
	Moderate: watchful waiting	**Moderate: self-management support by PN**
	Severe: referral to GP	Severe: referral to GP

##### Self-management support programme

The self-management support by the PN will be provided during extra 20-minutes consultations. Its aim is to teach patients to take responsibility for the day-to-day management of their diabetes and its consequences. This self-management support is based on the MPI. The intervention strategy has been derived from principles of learning theory and has been described elsewhere [24]. PNs will help patients to define problems and solutions themselves, applying the techniques of problem-solving and reattribution. Problem-solving consists of 7 stages that efficiently address psychosocial problems and their possible solutions [25]. It starts by creating a link between emotional symptoms and problems, and explaining the rationale of the treatment: resolution of the problems may lead to resolution of the symptoms (step 1).

Step 2 involves clarifying and defining the problem. The third step is to set achievable goals. Once an achievable goal has been set, the patient will be asked to brainstorm about all potential solutions (step 4). Step 5 involves considering the pros and cons and selecting a preferred solution. In step 6, the solution will be implemented in daily life, and step 7 involves evaluating the progress. The problem-solving approach can easily be understood by patients and can also easily be taught to practice nurses [25]. Patients with strong emotional involvement will be supported using the reattribution technique. This starts by exploring and defining the patient’s problem, after which the patient is challenged to link cognitions to behaviour. To this end, patients may keep a diary to record thoughts, behaviours and related feelings. After possibilities to alter specific behaviours have been explored, an action plan will be formulated indicating how the goals can be achieved [20]. If specific problems appear to be persistent and serious over time, action will be undertaken to provide more specialised care. PNs are instructed to refer these patients to the GP.

In the original MPI, the cognitive approach appeared to benefit more highly educated patients more than lower educated ones [18]. The SMS will be implemented in a region in the south of the Netherlands that is characterised by relatively low socio-economic status [26], so in order to increase the benefit for patients with low socio-economic status, we will put greater emphasis on the problem-solving technique during the training of PNs.

A flowchart of SMS is presented in Figure 1.

**Figure 1 F1:**
[figure not shown]
Flowchart for SMS intervention.

#### Implementation strategy 2: involvement of regional GP organisation

SMS will be implemented in one region in the south of the Netherlands. A group of 77 general practices (103 GPs) in the region, who collaborate in a GP organisation, was involved from the beginning of the SMS project, and they have prioritised the integration of SMS in the care for type 2 diabetes patients. The GPs are responsible for about 16,000 patients with type 2 diabetes mellitus. The region is characterised by relatively low socio-economic status, health status and life expectancy and substantial ageing of the population [26,27]. Based on earlier research findings we estimate that as many as 2400 patients with type 2 diabetes mellitus (15%) may suffer from emotional distress accompanied by problems of daily functioning [28].

#### Implementation strategy 3: financial support

The reimbursement of diabetes care in the Netherlands is regulated by means of diagnosis-treatment combinations (DTC), a Dutch variant of the Diagnosis Related Groups [29]. For each care group, health insurers’ purchase integrated care by negotiating a fixed price per patient per year. The elements of care with corresponding tariffs are defined in a shared care protocol. This is driven by the Dutch ‘care standard’ for diabetes [9], which is based on existing guidelines, protocols and performance indicators. During the study, a health insurance company will reimburse the extra time spent on SMS by practice nurses and GPs. The reimbursement will be integrated in the DTC for diabetes care.

#### Implementation strategy 4: training

The PNs in the intervention group will be trained to carry out SMS in three 8-hour training sessions. The training programme is based on a nurses’ training course that has been shown to be feasible, attractive and successful. PNs learn how to help patients identify their problems and set achievable goals [24]. The training programme will also focus on exploration skills. PNs will learn to use instruments to establish the severity of psychosocial problems in a stepped approach (first DFT and DS, and if appropriate further exploration using 4DSQ). The training sessions will take place in small groups, to facilitate active participation of the PNs, for example by role-play. These three training sessions will be followed up by booster sessions and telephone consultations, whose frequency will depend on the PNs’ needs. Booster sessions will be used to maintain and improve the PNs’ SMS skills. PNs will make audiotapes during consultations, which will be reflected on during booster sessions.

#### Implementation strategy 5: registration system for SMS

SMS will be integrated in the registration system that GPs and PNs use for diabetes care. The steps to be taken during the detection phase of SMS as well as the different stages of the self-management support by the PN are displayed in the regular registration system. PNs will record how patients rate their burden of diabetes (DFT), as well as their scores on the distress screener (DS). This information will be displayed at the next diabetes check-up. The system also helps PNs compute the outcomes of the 50-item Four-Dimensional Symptom Questionnaire (4DSQ). The PNs will also record the self-management support steps that are taken during each consultation, and the patients’ action plans.

### Evaluation of the implementation process

#### Design

A process evaluation will be done to analyse the facilitators and barriers regarding integration of SMS in routine care. We will gather quantitative and qualitative data about the intervention as an integral part of the routine diabetes care, as well as about the health professionals (PNs and GPs) and patients, and the impact of SMS on the practice organisation and the community [30]. How SMS has been implemented and received by the participants will be measured by means of the following concepts, as recommended by Saunders and colleagues [31]: fidelity, dose delivered, dose received, reach, recruitment and context. In addition, the costs of implementing SMS in routine care will be assessed. The process evaluation will include formative evaluation with respect to the new components of the clinical intervention, as these aspects may need to be refined or optimised to make them fit the local setting.

#### Variables and measurements

* Fidelity* refers to the extent to which SMS has been implemented as planned. At each diabetes consultation, the PNs will record which steps of the SMS protocol have been carried out. The outcomes on the DS, DFT and 4DSQ, the choices that have been made regarding further treatment and the patients’ action plans will also be recorded. The registration system also offers room for comments. PNs will be asked to give an explanation if they deviate from the SMS protocol.

*Dose delivered* is measured as the number of components of SMS per patient that have been carried out as intended. Data will be derived from the registration system.

*Dose received* includes two components: *satisfaction* and *exposure.*

Exposure refers to the extent to which participants (patients and health professionals) are actively engaged with the SMS programme and use the tools of SMS in daily practice. Engagement and satisfaction of participants will be measured among the providers (PNs and GPs) and among the patients.

PNs will be asked to complete an evaluation form after the training sessions, with questions about the clarity of wording of the components of the training course. With regard to the integration of SMS in routine diabetes consultations, issues discussed with PNs during booster sessions will be recorded during the follow-up period. This will provide qualitative information about the barriers and facilitators that PNs may experience. At the end of the follow-up period (one year after the SMS training course), we will develop a questionnaire including all the barriers and facilitators that have been discussed during the booster sessions. PNs will be asked to individually rate all these issues.

The engagement and satisfaction of GPs will be evaluated by means of self-administered questionnaires. All participating GPs from the intervention arm will be asked about their involvement in the SMS programme and their views on the impact of SMS for their practice.

How patients experience being involved in the SMS programme will be explored in detail by holding semi-structured interviews with a purposive sample of patients who have received the SMS from their PN. These interviews will be held during the follow-up period. The topics include patients’ experiences with the detection phase of SMS, the self-management support, the opportunities for and barriers to the implementation of their action plans in daily life, and their suggestions for improvement of the SMS. Interviews with patients will be audio-taped and transcribed verbatim.

*Recruitment* refers to the way we have approached and invited the PNs and GPs to become involved in the project to implement and evaluate SMS.

*Reach* refers to the participation rate and will be measured as the number of GPs and PNs who actually participated.

*Context* refers to the factors relating to the practice, the community, the social/political context, or other situational issues that affect either the implementation of SMS or its outcomes. To examine context issues in terms of the implementation and effect of SMS, we will draw up the minutes of meetings with the regional care group of general practitioners, the health insurer and our research team.

#### Cost evaluation

We will measure the direct costs of SMS. In addition to the training and booster sessions, these will include the time to integrate SMS in routine diabetes consultations. PNs will record the time they spend on each stage of the stepped SMS approach.

#### Data analysis

Data of the implementation study will be analysed by means of descriptive statistics.

The qualitative interviews with patients will be analysed by interpretative phenomenological analysis, a framework that can be used to develop in-depth descriptions of patients’ experiences. The purpose is to explore the patients’ perceptions of what is important in relation to SMS. We will abstract themes and cluster them for each case [32]. Abstracting and clustering of the themes will be done independently by two researchers.

### Clinical effect evaluation

#### Design

The effect evaluation of SMS involves a pragmatic 2-armed cluster-randomised controlled trial (cluster-RCT) with PNs as the unit of randomisation. Allocation concealment will be achieved by having an independent experienced research assistant perform a blockwise randomisation using a random number seed computer program. PNs (n = 46) will be assigned to an intervention group or control group at an allocation ratio of 1:1, after stratification into PNs working alone in a practice, PNs working in a team and PNs working in different practices. PNs working in the same general practice will be randomised to the same trial arm.

PNs in the intervention arm will be trained to apply SMS in addition to the usual care, which consists of 3-monthly diabetes check-ups according to the current guidelines [10]. PNs in the control arm will be instructed to provide usual care.

Patients with emotional distress and problems of daily functioning will be included in the effect evaluation. To maintain the balance between the intervention and control groups, a screening procedure will be carried out by the research centre. A self-administered postal questionnaire will be used to detect eligible patients.

Approval for this study has been obtained from the Medical Ethics Committee of Maastricht University/University Hospital Maastricht.

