#### Sample size calculation

Assuming an alpha of 0.05 and a beta of 0.90, an improvement in perceived daily functioning (defined as a score less than or equal to 4 on the Daily Functioning Thermometer (DFT), our primary outcome) at T12 occurring in 20% of the patients in the intervention group versus 5% of those in the control group requires at least a net number of 116 patients per arm (N = 232; 5 patients per practice nurse). It will be necessary to take account of a possible dependence between observations on patients of the same practice nurse. The intra-class correlation coefficient (ICC) is assumed to be 0.04, a median value for cluster-RCTs in the primary care setting [33]. Assuming a 30% loss to follow-up [17] we need to recruit at least 331 patients (8 per PN). Since participation in the screening procedure will not necessarily mean that patients also give informed consent for the effect evaluation, 10 consecutive patients for each PN will be invited to participate in the effect evaluation (N = 460).

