##### Background variables

Patient variables that will be reported are sex, age, year of diagnosis, treatment of diabetes (insulin therapy or tablets), marital status and education. Furthermore, we will record the age of the PNs, the number of PNs for diabetes management working in a general practice, as well as the educational background of the PNs.

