#### Data analysis of the effect evaluation

The effectiveness of SMS will be assessed by intention-to-treat analyses. The comparability of patients in the intervention and control groups regarding baseline characteristics and demographics will be described and tested for significant differences (t-tests and Chi-square tests). The average changes in DFT score will be calculated, as well as the number of patients that have DFT ≤4 after receiving SMS (T4 and T12). Separate scores will be calculated for the subscales of the secondary outcome measures. Changes in the primary and secondary outcomes between the intervention and control groups will be analysed using multilevel analyses (linear and logistic regression methods) as this will account for intracluster correlation among PNs. Multivariate regression analyses will be used to adjust the results for co-variables such as patient characteristics (age, sex, socio-economic status) and PN characteristics (age, educational background).

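### Practices are allocated as a whole, but the sample size and the multilevel analysis name clustering by practice nurse only; if patients of different nurses in one unit are correlated, power is overstated and standard errors are too small

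*Protocol article*

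**What the plan says.** All references are to the protocol article.

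- **Clinical effect evaluation, Design.** The trial is a "cluster-randomised controlled trial (cluster-RCT) with PNs as the unit of randomisation". The same paragraph adds that "PNs working in the same general practice will be randomised to the same trial arm". The strata are PNs working alone, "PNs working in a team and PNs working in different practices". The numbers are given in PNs: "PNs (n = 46) will be assigned to an intervention group or control group at an allocation ratio of 1:1".
- **Sample size calculation.** The only clustering considered is "a possible dependence between observations on patients of the same practice nurse", with an ICC of 0.04, 5 analysed patients per PN and 116 patients per arm.
- **Data analysis of the effect evaluation.** Multilevel linear and logistic regression is chosen "as this will account for intracluster correlation among PNs". No practice level is named.
- **Background variables.** The plan will record "the number of PNs for diabetes management working in a general practice", but no planning value for it appears anywhere.

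**The concern.** In a practice with two or more participating PNs, the PN cannot be the unit of randomisation if all PNs there must share an arm. The practice is allocated once and its PNs follow. The team stratum shows that such practices are expected. A PN who works in several practices can, under the same rule, tie those practices into a larger unit. Wherever this happens there are fewer than 46 independently allocated units.

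Patients of different PNs in one practice share the practice, its supervising GPs and the trial arm. In the intervention arm they also share local implementation of the programme. Some positive correlation between them is plausible. A design effect and a random effect at PN level treat these patients as independent. If the correlation is positive, the confidence interval for the primary comparison is too narrow, the type I error exceeds 5% and the planned power is not reached.

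**Working it through.** **Inputs from the article.** Response 20% versus 5%; alpha 0.05 (taken as two-sided, since sidedness is not stated); power 0.90 (the article prints this value as beta); ICC 0.04; 5 analysed patients per PN; 116 per arm; 30% loss; 46 PNs.

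**Inputs that are assumptions.** *k*, the number of PNs per allocated unit, and *r*, the correlation between patients of different PNs in the same unit. The article gives neither.

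**1. Reproduce the plan's figure.** Two proportions, pooled variance under the null, no continuity correction, mean proportion 0.125:

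n = [1.960 × √(2 × 0.125 × 0.875) + 1.2816 × √(0.20 × 0.80 + 0.05 × 0.95)]² / 0.15² = 100.06 per arm.

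Design effect with the PN as cluster: 1 + (5 − 1) × 0.04 = 1.16. Then 100.06 × 1.16 = 116.07, against 116 stated. In reverse, 116 / 1.16 = 100 effective patients per arm gives 90.0% power. For loss, 232 / 0.70 = 331.4, against 331 stated. The published sample size is thus the PN-level calculation, with nothing added for the practice.

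**2. Put the allocated unit in.** With *m* patients per PN, the design effect is

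DE = 1 + (m − 1) × 0.04 + m × (k − 1) × r.

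A PN-only model uses 1.16 at m = 5. The true standard error is therefore √(DE / 1.16) times the model's, and the two-sided error at nominal 5% is 2 × [1 − Φ(1.96 / that ratio)].

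At 116 per arm, m = 5:

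| k | r | DE | Effective n per arm | Power | SE ratio | Type I error, PN-only model |
|---|---|---|---|---|---|---|
| 1, or any k with r = 0 | – | 1.16 | 100.0 | 90.0% | 1.00 | 5.0% |
| 2 | 0.01 | 1.21 | 95.9 | 88.7% | 1.02 | 5.5% |
| 2 | 0.02 | 1.26 | 92.1 | 87.4% | 1.04 | 6.0% |
| 1.5 (weighted mean) | 0.04 | 1.26 | 92.1 | 87.4% | 1.04 | 6.0% |
| 2 | 0.04 | 1.36 | 85.3 | 84.8% | 1.08 | 7.0% |
| 3 | 0.04 | 1.56 | 74.4 | 79.6% | 1.16 | 9.1% |

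The weighted mean of 1.5 corresponds, for example, to half the PNs working solo and half in pairs.

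**3. Allow for the rounded recruitment target.** 331 / 46 = 7.2, which the article rounds up to 8 per PN. If 8 are recruited, 46 × 8 = 368, and 368 × 0.70 / 2 = 128.8 per arm are analysed, with m = 5.6. The same formulas give 89.8% power for k = 1.5 with r = 0.04 and for k = 2 with r = 0.02, 87.2% for k = 2 with r = 0.04, and 81.9% for k = 3 with r = 0.04. The larger m does not lower the type I error of a PN-only model: for k = 2 and r = 0.04, DE = 1.408 against 1.184, the SE ratio is 1.09 and the error about 7.2%.

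These figures use the normal distribution. They leave out the further loss of degrees of freedom from having fewer than 46 units.

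**The case against.** **The size is not known.** A reader might infer from the text that the standard errors are too small and the power overstated, full stop. The article does not support that. Both effects vanish if each unit has one PN or if r is zero. This objection stands, and the claim has to be conditional.

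**The larger figures are upper cases.** A reader might also take 80% power and 9% error as the expected outcome. That needs three PNs in every unit and a between-PN correlation equal to the whole ICC, so that the PN adds no clustering of its own. One stratum consists of PNs working alone. Implementation strategy 2 describes 77 practices with 103 GPs, about 1.3 GPs per practice, which does not suggest large nurse teams everywhere. This also stands, with a limit: the number of participating practices is not stated, and PNs covering several practices could enlarge the units.

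**There is some recruitment slack.** Meeting 8 per PN keeps power at about 90% in the moderate cases. This stands for power only. The margin comes from rounding, the stated requirement is at least 331, and it does not repair type I error. The 460 invitations are no reserve, because the article assigns them to non-consent.

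**The random-effects structure belongs in the SAP.** The analysis sentence does not say that PN is the only level, and this is a condensed article. That would answer a complaint about missing detail. Here, though, the article states the level of clustering in two places, and it is not the level at which its own rule allocates. Recording practice type and the number of PNs per practice does not replace a random effect.

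**Conclusion.** The point holds in conditional form. The same-arm rule makes the practice, or a linked set of practices, the allocated unit, and neither the sample size nor the stated analysis carries that unit. The direction is clear for any positive between-PN correlation within a unit.

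The magnitude depends on two quantities the article does not give. At 116 per arm the plausible range is from no change to about 85% power and 7% type I error, with 87–89% and 5.5–6% in the moderate cases; 80% and 9% is an upper case. The mismatch in the text is certain; the size of its effect is not. It should be fixed, because the model must match the allocation before outcome data are seen. It is not evidence that the trial is materially underpowered.

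**What to change.** 1. In Design, define the randomised unit as the general practice, or the set of practices linked by a shared PN.
2. In Data analysis of the effect evaluation, specify a random intercept for that unit with PN nested within it, or cluster on that unit.
3. In Sample size calculation, state the number of such units and their mean number of patients, recompute the design effect at that level and restate the power. Where the between-PN correlation is unknown, give a short range like the one above.

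Keeping practices intact at allocation is sensible and need not change. The cost is wording, one extra random effect and a possibly somewhat lower stated power. No more patients need to be enrolled.
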